## Abstract

**Introduction:**

Food retail outlets in sports and recreation facilities often fail to support healthy eating, despite aligning with healthy lifestyles and goals of local governments (LGs) that often own or manage them. LGs face barriers to implementing facility changes including inadequate staffing, training and incentives. The Promoting CHANGE initiative was co-designed to support LGs in improving and sustaining healthier food and drink offerings in these settings.

**Methods and analysis:**

A 3-year, type 2 effectiveness-implementation hybrid cluster randomised controlled trial will evaluate the Promoting CHANGE capacity-building and support package in three Intervention and four Control LGs in Victoria, Australia (August 2023–July 2026). The co-designed initiative includes human resource support, training, tools, technical assistance, community-of-practice groups, feedback based on food outlet audit and sales data and small grant incentives. Using the RE-AIM (Reach, Effectiveness, Adoption, Implementation, Maintenance) evaluation framework, the trial’s co-primary outcomes are the percentage of least healthiest food and drinks (1) displayed (implementation) and (2) sold weekly (effectiveness). Key secondary outcomes are effectiveness (sales and revenue); facility-level adoption, implementation, maintenance of healthy changes; cost-effectiveness (within-trial modelled economic evaluation). Findings will provide evidence of the initiative’s effectiveness and scalability, informing recommendations for advancing healthier food environments in over 6000 community-based food outlets across 500 Australian LGs, with implications globally.

**Ethics and dissemination:**

This study has received approval from the Deakin University Human Research Ethics Committee (reference number HEAG-H 92_2023). The results will be published in scientific peer-reviewed journals along with plain language summaries for participants.

**Trial registration number:**

ACTRN12621001120864.

STRENGTHS AND LIMITATIONS OF THIS STUDYThe Promoting CHANGE support package was co-designed with project partners using theory-informed and evidence-based implementation approaches, enhancing relevance and feasibility in real-world settings.The study employs a rigorous cluster randomised controlled trial using a type 2 hybrid design, allowing for simultaneous evaluation of intervention effectiveness and implementation processes.Integration of comprehensive six monthly audits and sales tracking provides robust, objective data on retail environment changes over time.Embedded economic and process evaluations strengthen the methodological framework by enabling in-depth analysis of implementation fidelity, costs and contextual factors.The potential for selection bias exists, as local governments with a pre-existing interest in nutrition may be more inclined to participate, which could limit generalisability.

## Introduction

 The health and economic burden of diet-related conditions such as obesity, type 2 diabetes and cardiovascular diseases underscores the urgent need to address unhealthy dietary consumption patterns in Australia^1^ and globally.^2^ The WHO recognises the pivotal role of physical, economic, political and socio-cultural surroundings in shaping dietary behaviours^3 4^ (collectively known as ‘food environments’^5^). In Australia, food retail outlets (henceforth ‘food outlets’) within sports and recreation facilities (henceforth ‘facilities’), such as cafés and kiosks (smaller, temporary or semi-permanent establishments), are often owned or managed by local governments (LGs). The role of LGs in advancing public health through localised action, including promoting healthier food retail environments,^3 6 7^ aligns with national strategies for obesity prevention and state-level and territory-level mandates.^8 9^ LGs can foster healthier food environments by implementing policies that enhance the availability and promotion of nutritious food and drink options,^10 11^ encouraging healthy sponsorships and partnerships and supporting health promotion initiatives for community well-being.^12 13^ Customer surveys have shown strong public support for providing healthier food and drink offerings in Australian LG settings,^14^,^16^ while council managers have expressed increased optimism in the value of these strategies following the implementation of a healthy beverage policy.^14^ However, despite the association of sports and recreation settings with healthy lifestyles, these facilities often do not support healthy eating.^17 18^ This paradox highlights the need for targeted interventions to transform these spaces into environments that align with public health objectives.

There is strong evidence that the healthiness of customer purchases can be improved by addressing the ‘4Ps’ of in-store marketing (‘product’ availability, ‘price’, ‘promotion’ and ‘placement’) to favour healthiest over least healthiest food and drink options.^10^ Three studies conducted in two Australian states have demonstrated that targeted interventions to improve the nutrition of retail food environments can increase customer purchases of healthier items in sporting clubs and in recreation centres.^19^,^21^ However, the impact of these initiatives on overall sales revenue has been mixed. One randomised controlled trial of a multicomponent intervention targeting the availability and promotion of non-sugar-sweetened drinks and fruit and vegetable products in sporting clubs found no change in overall food and drink sales.^19^ Similarly, a pre-post intervention observational study of the introduction of a healthy food and drink policy in recreation centres found no change in food sales revenue but noted a 27% decrease in drink sales.^21^ Another observational study with a pre-post design also in recreation centres that only focused on drinks found that the sugar-sweetened beverage reduction initiative resulted in a 24% reduction in overall drink sales.^20^ These mixed results of shorter-term interventions highlight a need for longer-term trials in LG settings (both sporting clubs and recreation facilities), employing a rigorous study design and focused on both food and drinks.

Key barriers to implementation, maintenance and scaling-up healthy food provision identified through systems mapping include the lack of (1) skilled human resource time; (2) skill and knowledge-based capacity to drive change at the retail level; and (3) incentives for change.^22^ An evidence-based implementation framework to facilitate large-scale change was co-designed with project partners, involving 15 government and non-government organisations, to create the multicomponent ‘Promoting CHANGE’ support package (the intervention), to be tested in a 3-year type 2 effectiveness-implementation hybrid cluster randomised controlled trial (henceforth ‘trial’). Promoting CHANGE stands for ‘Promoting Community Health And Nutrition, and Government Engagement’.

The following protocol aims to describe the Promoting CHANGE trial which aims to investigate the implementation and effectiveness of the intervention on the healthiness of the food environment and sales in LG-owned and influenced sports and recreation facilities. We hypothesise that compared with Control facilities, facilities implementing Promoting CHANGE will lead to a reduction in (1) the percentage of the least healthiest food and drink products available estimated from products on display (implementation) and (2) the percentage of the least healthiest food and drink products purchased per week (effectiveness).

## Methods and analysis

### Study design

A type 2 effectiveness-implementation hybrid^23^ trial will run for 3 years beginning August 2023. Participant recruitment was completed before trial start, and data collection is ongoing (year 2 of 3 complete), with evaluation to occur mid 2026–2027. There are no restrictions on the implementation of other interventions or initiatives during the trial period, both in the intervention and control groups. The RE-AIM framework^24^ will be used to assess the reach, effectiveness, cost-effectiveness, adoption, degree of implementation and maintenance (sustainment) of Promoting CHANGE. Cost-effectiveness of Promoting CHANGE will be assessed by a within-study trial and modelling long-term intervention effects. The project logic model is attached as online supplemental appendix I. This trial protocol is reported in line with the SPIRIT statement^25^ and the checklist can be found in online supplemental appendix II.

### Patient and public involvement

All project partners, including participating LGs, have been involved in the intervention and implementation framework design and dissemination.

### Study setting

LGs in Victoria, Australia typically own and/or manage sport and recreation facilities such as sporting stadiums, gyms and indoor and outdoor pools. The financial relationships between LGs and these facilities vary by governance model; some may be internally run or directly operated by LGs, or alternatively leased to external providers under contractual or management agreements. In cases where facilities are externally managed, lease and service agreements may include financial incentives, performance requirements or funding arrangements that influence operational decisions. Consequently, changes in funding structures, contractual incentives or LG policy mandates could plausibly affect facility-level outcomes, although the extent of this influence would depend on the specific governance and contractual arrangements in place.

Many of these facilities have food outlets including cafes, kiosks and vending machines to which the voluntary Victorian Government ‘Healthy Choices’ guidelines^26^ for sports and recreation centres^27^ (hereafter ‘the Guidelines’) apply. The Guidelines classify food and drinks as ‘GREEN’ (best choices), ‘AMBER’ (choose carefully) or ‘RED’ (limit). Full compliance requires at least 50% of food and drink items available (displayed) in stores to be ‘GREEN’ and less than 20% to be ‘RED’.^27^ The Guidelines include requirements for the product availability, placement, pricing and promotion of food and drinks. These Guidelines are poorly implemented to date in sport and recreation settings.^28^

### Eligibility criteria

To be eligible, each LG was asked to recruit a minimum of two non-seasonal sports and recreation facilities that operate at least 10 months annually, each of which must include at least one food outlet. In addition, the facility managers were required to agree in principle to several conditions: (1) confirmation that they had not already fully implemented healthy in-store changes in line with the Guidelines^26^; (2) willingness to make food retail environment changes if assigned to the Intervention group; and (3) commitment to providing itemised sales data. If assigned to the Intervention group, LG-level representatives had to agree to fund at least 1 day per week of project officer time (with the remainder of their salary to be funded via the grant), along with manager supervision in-kind, over the trial period.

### Recruitment

Eight LGs, including 44 eligible non-seasonal facilities (three to nine per LG), were recruited for participation in the trial via an Expression of Interest process distributed to all 79 Victorian LGs with our partner networks between March and September 2021. LGs had the option to recruit additional facilities such as seasonal sporting clubs or non-seasonal libraries, arts centres and community centres to participate in the trial; however, these facilities would not be included in the evaluation of Promoting CHANGE. Recruitment occurred prior to a successful application for a federal government Partnership Project Grant from the Australian National Health and Medical Research Council (NHMRC).

### Intervention

A 3-year intervention was designed to support LG facilities towards compliance with the Guidelines. Components of the intervention were informed by a theoretical analysis of implementation determinants based on the Consolidated Framework for Implementation Research constructs,^29^ researchers’ previous experience and pilot studies^30^ and best-practice recommendations for multicomponent interventions from the Expert Recommendations for Implementing Change.^31^
Figure 1 shows the Promoting CHANGE support package components, figure 2 outlines when each of the components will be delivered during the trial and each component is described in detail in online supplemental appendix III within a Tidier table.^32^

**Figure 1 F1:**
[figure not shown]
Promoting CHANGE intervention support package delivered over the 3-year trial period.

**Figure 2 F2:**
[figure not shown]
Promoting CHANGE support package delivery, data components and study timepoints.

#### Human resource support

The key component of the Promoting CHANGE support package involves salary support for skilled LG project officers trained in health promotion and/or facility management to deliver tailored, localised facilitation strategies.^33^ Project officer salary support was budgeted as half a day per week per LG for administrative tasks, evaluation, policy development, training and other capacity-building exercises, along with an additional half a day per facility for delivering tailored support to the sports and recreation facility food outlet. Examples of healthy choices implementation support include choosing specific new products based on supplier availability in the LG area and food preparation facilities within the outlet; marketing strategies tailored to customer base, for example, school carnivals for outdoor pools, demography of patrons. Of this, LGs agreed to fund 1 day worth of salary support and all staff on-costs; the NHMRC grant will fund the remainder of staff time. During the third year of the trial, grant-supplied salary support will be reduced by half as the project moves towards a long-term maintenance phase as indicated in figure 2.

LG project officers will collaborate with facility staff and management to advance implementation of the Guidelines. This includes creating or modifying recipes, identifying healthier product options and suppliers, training facility staff in improving the healthiness of the food outlet, creating communication and promotional materials and conducting six monthly in-store audits and collecting sales data. Decisions regarding which aspects of the Guidelines to prioritise will be made jointly by LGs and facilities with guidance from the Australian National Nutrition Foundation’s Healthy Eating Advisory Service (HEAS). LGs will be encouraged to draft policies aimed at embedding long-term changes, such as lease agreements and mandating compliance with the Guidelines.

#### Capability enhancement

The support package encompasses training sessions tailored for LG project officers and other relevant LG staff, delivered by HEAS with support from the research team and project partners, grounded in best practice principles for Community of Practice.^34^ These interactive training sessions will cover a spectrum of topics including cross-sectoral planning, engagement, policy development, health promotion, business skills and in-store marketing. The tools and technical assistance offered by HEAS include guidance on product classification using HEAS’ online FoodChecker classification tool,^35^ support for healthy food retail implementation planning and troubleshooting through a Microsoft Teams forum plus periodic telephone check-ins and provision of curated implementation and evaluation tools.

#### Feedback based on food outlet audit and sales data

Feedback will be provided by the research team for the LG project officers to present to intervention facilities. Facilities will receive six monthly verbal and written visual feedback based on food outlet audits including the healthiness of food and drinks on display, as well as customer satisfaction outcomes during the trial (at T0, T3). LGs will also receive feedback annually on the percentage of ‘GREEN’, ‘AMBER’ or ‘RED’ food and drinks sold each week based on units sold and weekly sales revenue. See figure 2 for when feedback delivery will occur for progress monitoring.

#### Incentives

Each facility will have access to $A1000 as small equipment grants to make enhancements to their food outlet to encourage healthier customer purchases during the 3-year trial.

### Control group

Facilities within LGs assigned to the Control group will continue with their current practice during the trial period, given the nature of the randomised controlled trial. Following the conclusion of the trial, Control group LGs will be offered a condensed 1-year long high-intensity human resource support package including project officer recruitment, equivalent financial incentives distributed over 1 year, skills and knowledge enhancement opportunities at project officer and facility level, auditing and feedback, along with equipment grant incentives, as benefit for participating in the trial.

### Outcome measures

For the purposes of this study, primary outcomes were selected based on the key policy focus of the Guidelines for sports and recreation settings, where full compliance requires at least 50% of food and drink items available in stores to be ‘GREEN’, and less than 20% to be ‘RED’.^27^

#### Primary outcomes

Implementation: At each facility, percentage of least healthiest ‘RED’ food and drink products available will be estimated from the products on display at the time of the audit. Effectiveness: At each facility, percentage of least healthiest ‘RED’ food and drink product volume (kg or L) purchased per week will be calculated using weekly sales data.

#### Secondary outcomes

*Secondary* measures are reported in online supplemental appendix IV (Section 1).

### Sample size considerations

Power calculations for sample size were performed in PASS (V.16). They were based on the number of LGs recruited and the number of non-seasonal facilities that agreed to provide display and point-of-sale data used to evaluate the sales outcomes. This included 21 non-seasonal facilities in four LGs in the Intervention group and 14 facilities in four LGs in the Control group (mean n=5 and n=4 sites per LG, respectively). *Primary implementation outcome*: The trial will have 80% power to detect a mean difference between groups of ≥18.8% in the percentage of ‘RED’ drinks displayed at the end of the 3-year trial (intraclass correlation coefficient 0.05, cluster size variation coefficient 0.37, SD=17.8, α=0.05, 2-sided test).^16 30^ This effect size is similar to that observed in the Water in Sport project—an uncontrolled pre-post natural experiment conducted in sports and recreation settings in Victoria, Australia (−18.9% at 18 months).^16 30^
*Primary effectiveness outcome*: With 156 weeks of sales data, the trial will have 80% power to detect a difference of ≥9% between groups in the percentage of ‘RED’ drink weekly drink sales at the end of the 3 year trial, using a generalised estimating equation (GEE) model assuming linear trends^36^ (first-order autoregressive, AR(1) correlation structure, ρ=0.73, SD=13.7). This effect size is smaller than in Water in Sport (−11% at 2 years).^30^ As of December 2024, due to the drop-out of one recruited LG and the withdrawal of some individual facilities in other LGs, the trial involves three LGs in the Intervention group, with a total of 16 non-seasonal facilities, and four LGs in the Control group, with a total of 8 non-seasonal facilities.

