### Statistical methods

#### Primary outcomes

*Implementation*: Initially, the effect of Promoting CHANGE on each outcome will be assessed at the 3-year mark, using a GEE model^36^ to account for clustering within LGs, adjusted for facility characteristics. The GEE model framework will also be used to assess the effect of Promoting CHANGE on the six monthly outcomes over time.

*Effectiveness*: The effect of the intervention on the rate of change of weekly sales over the 3-year trial will be assessed using a GEE framework to account for autocorrelation in weekly trends over time. The model will include intervention, time and their interaction; facility as a fixed effect; and will adjust for weekly temperature and facility characteristics. Sensitivity analyses will also help handle any missing data. All analyses will be performed on an intention-to-treat basis, for all randomised participants for which there are available data.

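### On the printed inputs, the display co-primary's 80% power is reproduced only without LG-level degrees of freedom; with eight randomised LGs it is about 65%, unadjusted and unpaired

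*Protocol article*

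**What the plan says.** The Sample size considerations section of the protocol article gives the design behind the calculation: "This included 21 non-seasonal facilities in four LGs in the Intervention group and 14 facilities in four LGs in the Control group", summarised as "mean n=5 and n=4 sites per LG, respectively". For the display outcome (share of RED drinks on display at three years) it states: "The trial will have 80% power to detect a mean difference between groups of ≥18.8" percentage points. The inputs are "intraclass correlation coefficient 0.05, cluster size variation coefficient 0.37, SD=17.8, α=0.05, 2-sided test". The section compares this target with a reduction of 18.9 points seen in an earlier uncontrolled project and calls the two similar. On method it names only the software ("Power calculations for sample size were performed in PASS (V.16"); no test statistic or df is given.

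Under Randomisation and blinding, LGs are the units allocated: eight LGs, paired on location, socioeconomic index and number of facilities, and randomised within pairs. Under Statistical methods, the display outcome at three years is to be analysed by GEE "to account for clustering within LGs, adjusted for facility characteristics".

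**The concern.** The calculation allows for clustering through the ICC and the variation in cluster size. That sets the size of the standard error. It does not settle how well the standard error can be estimated, which depends on the number of randomised units. With four LGs per arm, an analysis that respects clustering within LGs has few df for its variance, and a two-sided 5% test needs a critical value well above 1.96. If the power figure leaves this out, it is too high even at full planned size, before any drop-out.

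Display is a co-primary outcome. An overstated power makes a non-significant display result look more informative than it is, and it makes the detectable difference appear to match the cited benchmark. An update for the present sample that used the same approach would carry the same overstatement.

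**Working it through.** **Inputs** (all from Sample size considerations): facilities 21 and 14; LGs 4 and 4; ICC 0.05; cluster-size CV 0.37; SD 17.8; two-sided α 0.05; difference 18.8 points.

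**Standard error.** Design effect per arm: DE = 1 + [(CV² + 1)m − 1] × ICC, where m is the mean number of facilities per LG.

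- Intervention, m = 21/4 = 5.25: DE = 1 + (1.1369 × 5.25 − 1) × 0.05 = 1.248
- Control, m = 14/4 = 3.5: DE = 1 + (1.1369 × 3.5 − 1) × 0.05 = 1.149
- SE = 17.8 × √(1.248/21 + 1.149/14) = 17.8 × √0.1415 = 6.70
- Standardised difference = 18.8/6.696 = 2.81

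With the rounded 5 and 4 sites per LG (20 and 16 facilities), the design effects are 1.234 and 1.177, the SE is 6.55 and the standardised difference is 2.87.

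**Reproducing the stated figure, then changing only the reference distribution.** The normal detectable difference is (1.960 + 0.842) × SE. The t rows use the noncentral t.

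| Reference | Power at 18.8, 21 v 14 | 80% detectable, 21 v 14 | Power at 18.8, 5/4 sites | 80% detectable, 5/4 sites |
|---|---|---|---|---|
| Normal | 80.2% | 18.76 | 81.9% | 18.34 |
| t, facility df (33; 34) | 77.8% | 19.33 | 79.7% | 18.88 |
| t, LG df (4 + 4 − 2 = 6) | 65.1% | 22.55 | 67.0% | 22.04 |
| t, pairs (4 − 1 = 3), no precision gain from pairing | 48.5% | 28.5 | 50.1% | 27.9 |

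Two rows match the printed 80% and 18.8: normal with 21 v 14, and facility-level t with the rounded sizes. No LG-level row comes near 80%. With the ICC set to zero, the SE is 6.14 and power on 6 df is still only 72%, so most of the gap comes from the df and not from the ICC.

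**Simulation check.** This used 60,000 replicates at planned size. Individual LG sizes are not published, so three assumed splits summing to 21 and 14 were used. Cluster-level t tests on 6 df held 4.9–5.2% type I error and had 62–66% power at 18.8 points. A GEE with an uncorrected sandwich variance and a normal reference showed 86–87% power, but with 14–16% type I error.

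**Current sample** (3 LGs with 16 facilities v 4 LGs with 8), assuming ICC, CV and SD are unchanged: DE 1.253 and 1.064, SE 8.18. Normal: 63% power, 22.9 points detectable. t on 3 + 4 − 2 = 5 df: 46% power, 28.8 points detectable.

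**The case against.** The article's arithmetic is sound on its own terms: 80% follows from the inputs under either of two conventional references. The dispute is over the choice of reference. A reader might infer that a normal formula was certainly used. The article does not say so, and a facility-level t test with the rounded cluster sizes fits almost as well. What stands is narrower: neither calculation that fits uses LG-level df.

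A reader might also infer that 80% power and a 5% level cannot coexist in this design. The documents do not support that. The planned GEE adjusts for facility characteristics, and on 6 df the 80% at 18.8 points would be recovered if adjustment removed about 30% of the variance (27% with the 5/4 sizes). The article claims no such gain in its power calculation, so this cannot support the printed figure, but it could be argued openly.

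Nor is 65% the one true power. It belongs to an unpaired, unadjusted comparison. Randomisation was within four pairs, and a matched analysis would have 3 df, with power depending on what pairing removes.

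Finally, a small-sample correction for the GEE may well be specified in an analysis plan that is not shown, and its absence from the article is no fault. Such a correction would protect the 5% level. It would not bring back the 80%.

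Recruitment is complete, so restating the power changes neither design nor data. It changes how the result should be read.

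**Conclusion.** The concern holds in this form: on the printed inputs, 80% power for 18.8 points at two-sided 5% is obtained only when LG-level df are left out. With eight randomised LGs, an unadjusted, unpaired test that holds its level has about 65% power (roughly 62–67% depending on LG sizes). About one in three true effects of that size would be missed at full planned size. The difference detectable with 80% power is about 22–22.5 points, which exceeds the 18.9-point benchmark. A matched-pair analysis on 3 df would have about 49% if pairing brings no precision.

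These figures take the ICC, CV and SD as printed and assume no gain from covariates. The shortfall is separate from drop-out. At the current 3 v 4 LGs, the same approach gives about 46% power and about 29 points, on the further assumption, which the documents do not support, that ICC, CV and SD carry over to the smaller sample. Part of that fall is attrition: on LG-level df, power goes from 65% to 46%.

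**What to change.** Recompute the display power with a t reference on LG-level df that matches the planned analysis, and name the test and df in the sample-size paragraph. For an unadjusted, unpaired comparison at planned size, the restated figures are about 65% power for 18.8 points, or 80% power for about 22.5 points. If the analysis is to be paired, or to rely on precision from covariates, state that and the variance reduction assumed.

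Reword the benchmark comparison, since on these df the detectable difference is larger than the cited 18.9 points. Say that the display result will be interpreted by its confidence interval.

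Any update for the current sample should use the same approach (5 df if unpaired), state that ICC, CV and SD are assumed unchanged, and report the loss from drop-out separately.

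The cost is a recalculation and a few sentences. No further LGs, facilities or data are needed. The drawback is a less favourable stated power.

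### Both primary-outcome power statements are for RED drinks only, so the power for the RED food-and-drink outcomes to be tested is not stated

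*Protocol article*

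**What the plan says.** Three parts of the protocol article define the primary outcomes on food and drink together.

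- Abstract, Methods and analysis: "co-primary outcomes are the percentage of least healthiest food and drinks (1) displayed (implementation) and (2) sold weekly (effectiveness".
- Introduction, the hypotheses: the first concerns "the percentage of the least healthiest food and drink products available estimated from products on display (implementation", and the second concerns the same products as purchased per week.
- Outcome measures, Primary outcomes: "percentage of least healthiest ‘RED’ food and drink products available will be estimated from the products on display at the time of the audit" for implementation, and "percentage of least healthiest ‘RED’ food and drink product volume (kg or L) purchased per week will be calculated using weekly sales data" for effectiveness.

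Sample size considerations has one power statement under each primary-outcome label. The implementation statement is for RED "drinks displayed at the end of the 3-year trial": 18.8 points, SD 17.8, ICC 0.05, cluster-size coefficient of variation 0.37, two-sided alpha 0.05. The effectiveness statement is for the RED share of "weekly drink sales at the end of the 3 year trial": 9 points, 156 weeks, AR(1) with correlation 0.73, SD 13.7. Both effects are compared with the Water in Sport project (−18.9% and −11%), which the Discussion describes as implementing healthy drink policies.

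**The concern.** The power statements carry the names of the primary outcomes but use a different variable. For display, the drinks share is only one component of the outcome. For sales, the denominator changes as well, from food and drink volume to drink sales. The article gives no SD, ICC, autocorrelation or expected effect for food, or for food and drink together. It does not say that drinks stand in as a proxy, and it does not argue that the drink values carry over.

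What is at stake is how the result is read. A null finding on RED food and drink would be judged against an 80% figure that was never calculated for it. The article's own Introduction gives a reason not to assume that the two behave alike: it calls for trials covering both food and drinks, and it cites a recreation-centre policy study in which drink sales fell by 27% while food revenue did not change.

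**Working it through.** **Inputs.** All come from Sample size considerations: 21 facilities in four intervention LGs and 14 in four control LGs (mean 5.25 and 3.5 per LG), and the SDs, ICC, coefficient of variation and AR(1) correlation listed above. Normal approximation; two-sided alpha 0.05, which the article states for display and which I assume for sales. The sum of the normal quantiles for 80% power is 1.960 + 0.842 = 2.802.

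**Display: reproducing the stated figure (drinks).**

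- Design effect = 1 + ((CV² + 1)m − 1) × ICC.
- Intervention: 1 + (1.1369 × 5.25 − 1) × 0.05 = 1.248. Control: 1 + (1.1369 × 3.5 − 1) × 0.05 = 1.149.
- SE = SD × √(1.248/21 + 1.149/14) = SD × 0.3762. At SD 17.8, SE = 6.70.
- Minimum detectable difference = 2.802 × 6.70 = 18.76 (stated: 18.8).
- Power at 18.8 = Φ(18.8/6.70 − 1.96) = 0.80.

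**Sales: reproducing the stated figure (drinks).**

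- Generalised least-squares variance of a linear slope over 156 weekly points, AR(1) with 0.73, slope scaled to the full three years. Per facility, the SE is 0.663 × SD.
- SE of the group difference = 0.663 × SD × √(1/21 + 1/14) = 0.2287 × SD. At SD 13.7, SE = 3.13.
- Minimum detectable difference = 2.802 × 3.13 = 8.78 (stated: 9).
- Power at 9 = Φ(9/3.13 − 1.96) = 0.82.

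Both figures reproduce, so the sums are sound for the drinks variables that they name.

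**Dependence on the missing food-and-drink inputs.** The SDs below, other than 17.8 and 13.7, are assumptions. Facility numbers, ICC and AR(1) correlation are held at the stated values.

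| Display SD | Minimum detectable difference | Power at 18.8 points |
|---|---|---|
| 12 | 12.6 | 0.99 |
| 15 | 15.8 | 0.91 |
| 17.8 (stated, drinks) | 18.8 | 0.80 |
| 20 | 21.1 | 0.70 |
| 25 | 26.3 | 0.52 |

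| Sales SD | SE | Power at 9 points |
|---|---|---|
| 10 | 2.29 | 0.98 |
| 13.7 (stated, drinks) | 3.13 | 0.82 |
| 20 | 4.57 | 0.50 |

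The effect size matters as much. With the SD kept at 17.8, display power is 0.61 for 15 points and 0.43 for 12. With the SD kept at 13.7, a 4.5-point sales effect has about 0.30.

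**Why the direction cannot be fixed.** Suppose that the combined display share is an equal mix of a drinks share and a food share, each with SD 17.8 and with correlation r. Its SD is then 17.8 × √((1 + r)/2). If food moves half as much as drinks, the combined effect is 0.5 × 18.8 + 0.5 × 9.4 = 14.1 points. Power is 0.56 at r = 1, 0.68 at r = 0.5 and 0.85 at r = 0. A diluted effect can therefore still leave more than 80% power if the SD falls too. The half-and-half split, the halved food effect and r are all illustrative.

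**The case against.** The strongest reply is that the calculation contains no error, and that drinks were the part of the outcome for which the authors had earlier data. That is true of the arithmetic. It would be a fair defence if the article called drinks a proxy and argued for the transfer, but it does neither.

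A second reply is that the unit, kg or L, may mean that food and drinks are analysed separately. The stated power would then belong to the drinks part, but the food part would have no power statement at all. The mismatch survives either reading.

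A third is that the sample is fixed: recruitment is complete and two of the three years are done, so a new figure cannot change the design. That stands, and it limits the remedy to a correction of what is reported and of how the result is interpreted.

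A reader might also infer that the trial is underpowered for its primary outcomes, because drinks are easier to substitute than food and the drinks effect would be diluted. The documents do not support that. Nothing in them says that RED food shares respond less than RED drink shares, and the contrast in the Introduction concerns sales revenue. Dilution also lowers power only if the SD does not shrink with it, as the mixture calculation shows. Nor should the loss of an LG and of individual facilities by December 2024 be counted here: it reduces power for any outcome and is a separate matter.

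**Conclusion.** The point holds as a mismatch between the powered variable and the tested variable, and it affects both co-primary outcomes. The stated 80% belongs to RED drinks. Power for RED food and drink is unstated, and no single corrected value can be computed from the article.

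The uncertainty is wide: at the planned size, roughly 52% to 91% for an 18.8-point display difference over SDs of 25 to 15, and 50% to 98% for a 9-point sales difference over SDs of 20 to 10. These ranges rest on assumed SDs, the normal approximation and the stated ICC and AR(1) correlation. They show sensitivity and do not estimate the true power. Neither low nor adequate power is demonstrated for the actual outcomes.

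**What to change.** 1. Label the two figures in Sample size considerations as applying to RED drinks only. If drinks are intended as a proxy for food and drink, say so and justify it.
2. Restate power, or the minimum detectable difference, for RED food and drink. For display, take the SD and ICC from the T0 food-and-drink audits, pooled over arms. For sales, take the SD and autocorrelation from baseline or early sales data, pooled over arms. Baseline data are preferable where they exist, because pooled early-trial sales would absorb any early intervention effect into the SD.
3. Give a sensitivity range over SD, ICC and effect, since an ICC estimated from seven LGs will be imprecise.
4. Read any null result on the primary outcomes against the restated figure.
5. Report drink and food shares beside the combined share, if supplemental appendix IV (not shown) does not already provide for this.

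The cost is one recalculation, which the T0 audits and the annual sales returns should allow, and a few lines of text. Pooling over arms means that no comparison between arms is seen. The downside is that the restated power may be less favourable than 80%.
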